### Data collection and measures

All measures for this study were selected to assess distinct constructs in our Adapted Pearlin’s Stress-Health Process Model of Family Caregiving (Fig. 3) and are listed and described in Table S1 (see Additional file 1). Measures are collected at baseline and every 12 weeks thereafter until the patient’s death or study end (data collection forms available upon request). For each time point, paper-and-pencil questionnaires are mailed to participants for them to complete and return in a prepaid, preaddressed envelope. Participants are subsequently paid via a Mastercard debit card at an escalating incentive amount per time point to enhance retention: $40 for baseline, $50 for 12 weeks, and $60 for 24 weeks. For every 12-week time point after that, participants receive $30.

After participants complete the questionnaire, surveys are returned in postage paid, preaddressed envelopes where data collection coordinators double-key enter de-identified survey responses into REDCap. REDCap is software for building and managing questionnaires and facilitating electronic data collection and storage [37]. It supports a HIPAA best practice, secure web-based application. Hard stops prevent missing data due to inadvertent skipping of items. This database is accessed on a secure network server that is password protected. Descriptive statistics will be used to conduct quality control on the preliminary datasets and identify missing/extreme data values. Study coordinators who have received intensive training (typically 10 h including role play and inter-rater reliability checks) will assure high-quality data collection from participants.

### Safety monitoring committee

This is a two-site study that has been deemed low risk, and hence, there are no planned interim analyses and a Data Safety and Monitoring Board is not appointed. However, the informed consent process, the recruitment process, and the timeliness and quality of the data will be monitored by the principal investigator, the WIRB Institutional Review Board, and a Safety Monitoring Committee (SMC). The SMC provides safety oversight and annual auditing and is composed of individuals with clinical trial, human subjects, and statistical expertise. The two co-chairs of the SMC are independent from study conduct and free of conflict of interest. The SMC meets annually to assess effectiveness data from each arm of the study (blinding is maintained). A SMC report is provided to the IRB on an annual basis.

### Statistical analysis plan

An intention-to-treat (ITT) approach will be used for analyses of Aims 1 and 2. Primary data analysis will begin with baseline descriptive statistics for baseline caregiver and patient characteristics and outcomes. The balance between study groups will be examined with respect to baseline characteristics using effect sizes. Conceptually relevant baseline factors showing non-trivial imbalances between groups will be used as adjusting covariates in longitudinal comparisons using linear mixed-effect modeling. Distributional assumptions will be examined, and when appropriate, we will employ inferential and modeling procedures robust to distributional assumptions.

#### Power analysis and sample size determination

Key considerations in our power analysis included (1) longitudinal modeling [49] with baseline and two follow-up time points (weeks 12 and 24 post-baseline); (2) 80% power to detect a mean difference in change; (3) a significance level adjusted with a false discovery rate approach (5% FDR) with relevant effects on 50% of outcomes, i.e., *α* = .025; (4) intra-subject correlation of *ρ* = .5 among repeated measurements; (5) minimal clinically important difference (MCID) for the primary outcomes, HADS-Anxiety and HADS-Depression scales of 1.5 points estimated from an adult population with psychological distress but no chronic disease, such as caregivers; and (6) standardized MCID of *d* = .37, using the HADS standard deviations (SD~3.9) from our prior Cornerstone study. Under these assumptions, with a sample size of *n* = 103 per study group, the detectable difference is *d* ≈ .37; however, a sample size of *n* = 120 per group allows additional power and precision for secondary analyses including comparisons of patient outcomes and exploratory analyses. Target recruitment is *N* = 294 FCGs (*n* = 147 per study group) to account for a possible dropout of up to 37.7% observed among caregivers enrolled in one of our prior trials (computations conducted with PASS v14 software).

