**Methods:**

This is a 2-site, single-blind, hybrid type I implementation-effectiveness trial of the Cornerstone intervention versus usual care. Cornerstone is a multicomponent intervention based on Pearlin’s Stress-Health Process Model where African American and/or rural-dwelling family caregivers of patients with newly diagnosed advanced cancer (target sample size = 294 dyads) are paired with a lay navigator coach and receive a series of six, brief 20–60-min telehealth sessions focused on stress management and coping, caregiving skills, getting help, self-care, and preparing for the future/advance care planning. Subsequent to core sessions, caregivers receive monthly follow-up indefinitely until the patient’s death. Caregiver and patient outcomes are collected at baseline and every 12 weeks until the patient’s death (primary outcome: caregiver distress at 24 weeks; secondary outcomes: caregiver: quality of life and burden; patient: distress, quality of life, and healthcare utilization). Implementation costs and the intervention cost effectiveness are also being evaluated.

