## Methods and design

### Study aims and hypotheses

The first aim of this hybrid type I randomized implementation-effectiveness trial is to test the effect of ENABLE Cornerstone on FCG outcomes over 24 weeks [30, 31]. Our primary hypothesis is that compared to usual care, intervention group caregivers will report lower distress as measured by the Hospital Anxiety and Depression Scale (HADS) over 24 weeks [32, 33]. Our secondary hypotheses are that compared to usual care, intervention group participants will report better quality of life (QOL) (PROMIS Global Health 10) and lower caregiver burden (Montgomery-Borgatta Burden Scale) over 24 weeks. The second aim is to test the effect of ENABLE Cornerstone on patient outcomes. We hypothesize that compared to usual care, patients of caregivers randomized to receive Cornerstone will report lower distress (HADS), better QOL (PROMIS Global Health 10), and lower healthcare utilization over 24 weeks [34, 35]. For our third aim, we are evaluating implementation costs and the cost effectiveness of Cornerstone implementation on caregiver and patient outcomes, including healthcare utilization. Finally, we have an exploratory aim to analyze mediators and moderators (e.g., resilience, social support effectiveness, preparedness) of the relationship between the intervention and caregiver and patient outcomes.

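### The primary endpoint is stated in three different ways, and 103 per group gives 80% power under some of these readings but not for an unadjusted change to week 24

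*Protocol article*

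**What the plan says.** The protocol article describes the primary endpoint in three places.

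- Abstract, Methods: "primary outcome: caregiver distress at 24 weeks". This is one outcome at one time point.
- Study aims and hypotheses: "intervention group caregivers will report lower distress as measured by the Hospital Anxiety and Depression Scale (HADS) over 24 weeks". This covers a period, and no subscale is named.
- Power analysis and sample size determination: "minimal clinically important difference (MCID) for the primary outcomes, HADS-Anxiety and HADS-Depression scales of 1.5 points". Here there are two primary outcomes. The target is "80% power to detect a mean difference in change", in a longitudinal model with "baseline and two follow-up time points (weeks 12 and 24 post-baseline". The time to which change is measured is not given.

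The power section concludes that 103 per group detects d of about .37, and adopts 120 per group for extra power and precision. The Statistical analysis plan section specifies linear mixed models. It takes as covariates those baseline factors that are conceptually relevant and turn out to differ noticeably between the groups. It does not say that baseline HADS is always adjusted for.

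**The concern.** The three statements differ in the number of outcomes (one or two), the timing (week 24 or the whole period) and the quantity compared (a level or a change). These are different tests with different variances, so one sample size cannot carry the same power for all of them. A reader who combines the abstract's week 24 with the power section's change would take the primary test to be change from baseline to week 24. At stake are whether the quoted 80% belongs to the endpoint the abstract announces, and whether a reader of the results can tell which comparison was the primary one.

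**Working it through.** **Inputs.** From the power section: d = .37, alpha = .025, power 80%, within-person correlation ρ = .5, 103 and 120 per group, SD about 3.9, and a minimal important difference of 1.5 points. From Randomization and blinding: 1:1 allocation. Two assumptions are mine, because the article does not state them: alpha is two-sided, and ρ is the same for every pair of visits (compound symmetry).

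**Formula.** n per group = 2V(2.2414 + 0.8416)² / d², where V is the variance of the contrast within a group, relative to the variance of a single HADS score. With d = .37 this is 2V × 9.505 / .1369, or about 138.9 × V. Power at a given n is Φ(d / √(2V/n) − 2.2414).

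**Variance factors at ρ = .5**

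| Contrast | V | n for 80% | Power at 103 | Power at 120 |
|---|---|---|---|---|
| Mean of weeks 12 and 24, minus baseline | (1+ρ)/2 + 1 − 2ρ = .75 | 104.1 | 79.5% | 85.7% |
| Week 24, adjusted for baseline HADS or with baseline means constrained equal | 1 − ρ² = .75 | 104.1 | 79.5% | 85.7% |
| Change from baseline to week 24, unadjusted | 2(1−ρ) = 1.00 | 138.9 | 66.1% | 73.4% |
| Linear slope over the three visits, expressed over 24 weeks | 4 × (1−ρ)/2 = 1.00 | 138.9 | 66.1% | 73.4% |

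**The article's own figure.** At V = .75 and n = 103, the detectable difference is 3.083 × √(1.5/103) = .372, which matches the stated .37. The required n, 105 after rounding up, is within about 2% of 103. The stated figure is therefore reproduced by the first two rows.

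**The other reading.** At V = 1.00 the requirement is 139. The detectable difference at 103 is 3.083 × √(2/103) = .430, or .430 × 3.9 = 1.68 points, above the article's 1.5-point threshold.

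**Sensitivity of the V = 1.00 result**
- The article's 1.5 points and SD of 3.9 imply d = 1.5/3.9 = .385 rather than .37. The requirement is then 129 per group, with power 69.8% at 103 and 77.0% at 120.
- A one-sided alpha of .025 gives 115 per group, which also fails to reproduce 103.
- Using the t distribution changes little: 65.4% instead of 66.1% at 103, and 79.0% instead of 79.5% for the V = .75 contrasts.

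**The case against.** The best defence is that the power section refers to longitudinal modelling with both follow-up visits, and that its number fits a change contrast averaged over them. The reading that reproduces the number should be preferred to one that does not. The size adopted is 120, where that contrast has 85.7% power. The exact contrast and the handling of baseline are matters a condensed article may leave to the statistical analysis plan. HADS-Anxiety and HADS-Depression are the scales of the HADS named in the aims, and a false-discovery-rate approach across outcomes is stated.

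Much of this stands. Two stronger conclusions that a reader might infer are not supported:

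- **That the sample size is wrong or the trial underpowered.** The article nowhere says that 103 is for an unadjusted change to week 24. For an averaged change or a baseline-adjusted week-24 comparison, 103 is correct.
- **That success will be claimed on whichever version is significant.** Nothing in the article states this. A multiplicity approach is described, and an unseen analysis plan may settle the choice.

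The defence does not remove the conflict. If the averaged change is what was powered, then the abstract's week-24 endpoint is not. This is disagreement between statements in the article, not detail left for later. The covariate rule is also stated, and it makes adjustment depend on observed imbalance.

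**Conclusion.** The point holds in a limited form. The primary endpoint is inconsistent across the abstract, the aims and the power section in number of outcomes, timing and contrast. The 103 per group is sound arithmetic for a contrast with variance factor .75, but not for an unadjusted week-24 change or a linear slope. The wording permits those readings without stating them. Between the two groups of readings, power runs from 79.5% to 66% at 103 per group and from 85.7% to 73% at 120. With d = .385 the lower figures become about 70% and 77%. For the week-24 endpoint, the stated 80% depends on accounting for baseline HADS, which the imbalance-triggered rule does not guarantee. All figures assume two-sided alpha .025 and compound symmetry with ρ = .5, and take 103 and 120 as evaluable caregivers.

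**What to change.** State one primary time point and one contrast, in the same words, in the abstract, the aims and the power section. One version that keeps the abstract's timing and the stated power is the week-24 group difference in HADS-Anxiety and in HADS-Depression from the mixed model, with baseline HADS always accounted for. There are two ways to do this: enter baseline as a covariate with weeks 12 and 24 as the outcomes, or keep all three visits as outcomes and constrain the baseline means to be equal between groups. Either way, exempt baseline HADS from the imbalance-triggered covariate rule. Choosing the average over weeks 12 and 24 would be equally coherent, provided the abstract is changed to match.

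Say also whether success requires one scale or both under the stated alpha. If an unadjusted week-24 change is kept, restate the power as about 66% at 103 and 73% at 120 per group.

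The cost is wording only: no extra participants, visits or measures. The article keeps the allocation sequence concealed until the last participant completes 24-week data collection and the data have been checked, so the choice can be fixed and dated before then.

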The original ENABLE early palliative care caregiver intervention was tested in a New England population of advanced cancer caregivers [23, 24]. While these results showed that intervention group caregivers had lower depressive symptoms and stress burden, the trial sample included nearly all white individuals and the intervention was led by advanced practice nurse coaches. To adapt this early palliative care intervention to a more historically under-resourced and racially diverse population and leverage a more available workforce, we completed a qualitative formative evaluation study with caregivers and patients of rural and minority populations in the Southern U.S. employing lay oncology navigators [28]. After eliciting and incorporating participant feedback, a new version of the ENABLE Caregiver intervention was developed called ENABLE Cornerstone. ENABLE Cornerstone was subsequently evaluated for feasibility, acceptability, and potential efficacy in a small-scale, pilot randomized trial (intervention vs. usual care) with 63 African American and/or rural-dwelling FCGs (November 2019 to March 2021) [22]. This pilot demonstrated high acceptability and data collection completion rates. In addition, the preliminary efficacy scores for mitigating distress were promising for both Cornerstone caregiver participants and their care recipients. Hence, we are now conducting a fully powered randomized trial of the Cornerstone intervention. This manuscript describes the conceptual foundations of Cornerstone and the clinical trial design.

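### At the stated 37.7% dropout, 147 per group leaves about 92 completers, fewer than the 103 behind the 80% power statement; 147 covers only about 30% dropout

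*Protocol article*

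**What the plan says.** All the figures are in the protocol article, under Power analysis and sample size determination.

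- The design goal is "80% power to detect a mean difference in change", with "a significance level adjusted with a false discovery rate approach (5% FDR) with relevant effects on 50% of outcomes, i.e., *α* = .025" and "intra-subject correlation of *ρ* = .5 among repeated measurements".
- The effect is a "standardized MCID of *d* = .37, using the HADS standard deviations (SD~3.9) from our prior Cornerstone study".
- The resulting size is given as "with a sample size of *n* = 103 per study group, the detectable difference is *d* ≈ .37".
- A larger size of 120 per group is then preferred, for extra power and for precision in secondary and exploratory analyses.
- Recruitment is finally set at 294 caregivers, 147 per group, "to account for a possible dropout of up to 37.7% observed among caregivers enrolled in one of our prior trials".

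The Abstract and the Overview of the study design repeat the 294 target, and the Overview treats the 147 as caregivers randomized to each arm. Under Recruitment, randomization takes place only after the completed baseline survey has come back. The article gives no other dropout rate and does not show how 147 follows from 37.7%.

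**The concern.** A recruitment target said to account for a dropout rate should leave the required number of completers once that rate is applied. Here it does not. Because caregivers are randomized after returning the baseline survey, the allowance cannot be read as loss before randomization; it has to cover loss afterwards.

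What is at stake is a stated property of the design. Readers, the IRBs and the Safety Monitoring Committee would take from this sentence that the trial keeps its planned size even if attrition reaches the level seen in the team's own earlier trial. On the article's own numbers, the completers would then be fewer than the number the power statement needs.

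**Working it through.** **Inputs** (all from the power section): power 80%; α = .025, taken as two-sided because that reproduces the stated size; d = .37; ρ = .5; baseline plus weeks 12 and 24; 103, 120 and 147 per group; dropout 37.7%.

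**1. Reproduce the 103.** The article does not print its formula. For the mean of two follow-ups minus baseline, with equal correlation ρ, the variance factor is (1 − ρ)(1 + 1/2) = 0.5 × 1.5 = 0.75. Then

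n = 2 × 0.75 × (2.2414 + 0.8416)² / 0.37² = 1.5 × 9.505 / 0.1369 ≈ 104.1 per group, or 105 when rounded up with a small-sample convention.

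This is within 3% of 103, so the base size is consistent with the stated inputs. A change score at one follow-up alone (factor 1.0) would need about 139. The 103 therefore already relies on both follow-ups.

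**2. Apply the stated dropout to 147.** 147 × (1 − 0.377) = 91.6 per group (294 × 0.623 = 183 in total). This is below 103 and below 120.

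**3. Try to reach 147 from 37.7%.**

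| Starting size | n / (1 − 0.377) | n × 1.377 |
|---|---|---|
| 103 | 166 | 142 |
| 120 | 193 | 166 |

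Neither the correct inflation nor the common mistaken one gives 147.

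**4. Dropout that 147 does cover.** For 103: 1 − 103/147 = 29.9%. For 120: 1 − 120/147 = 18.4%.

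**5. Power if dropouts contribute no follow-up data.** Power = Φ(d × √(n / 1.5) − 2.2414), with d = .37:

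- n = 91.6: Φ(2.891 − 2.241) = Φ(0.650) = 74%
- n = 103: 79.5%
- n = 120: 86%

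**6. Power if some dropouts return week 12.** A caregiver with baseline and week 12 only has variance factor 2(1 − ρ) = 1.0, against 0.75 for a completer. Such a caregiver therefore carries 0.75 of a completer's information, assuming a constant effect over follow-up and known covariance. With 147 × 0.377 = 55.4 dropouts per group and a share q of them supplying week 12, the completer-equivalent size is 91.6 + 0.75 × 55.4 × q.

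| q | Equivalent n per group | Power for d = .37 |
|---|---|---|
| 0 | 92 | 74% |
| 25% | 102 | 79% |
| 50% | 112 | 83% |
| 75% | 123 | 87% |
| 100% | 133 | 89% |

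The stated 103 is reached at q = (103 − 91.6) / 41.6 ≈ 27%. The formula's own 104.1 for 80% power is reached at about 30%.

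**The case against.** The strongest objection is that the loss of power is not certain. The article plans an intention-to-treat analysis with linear mixed-effect modelling, and its power calculation is longitudinal. A caregiver lost after week 12 still contributes. As step 6 shows, power at 37.7% dropout could be anywhere from 74% to 89%. This stands, and it limits the consequence. It does not rescue the sentence: the article claims no such credit, gives no timing of dropout, and states the primary outcome as distress at 24 weeks in the Abstract but over 24 weeks in the aims. The credit depends on a constant effect across both follow-ups.

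It can also be said that 37.7% is an upper bound from one prior trial, not the expected rate. That is fair, but the sentence says the target covers that upper bound.

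Some stronger readings are tempting, and the documents do not support them:

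- *That the trial falls below 80% power at 37.7% dropout as a matter of fact.* This is only the case in which few or no dropouts return week 12.
- *That the 80% power statement also rests on 120.* It rests on 103 alone; 120 is offered for additional precision.
- *That the trial could no longer detect its clinically important difference.* With no partial data the detectable d is about .395, or 1.54 points at SD 3.9, against an MCID on the "HADS-Anxiety and HADS-Depression scales of 1.5 points estimated from an adult population with psychological distress". The gap is 0.04 points with an SD that is itself approximate. At 1.5/3.9 = .385 the same formula gives about 78% power.
- *That the patient analyses lose their margin.* The 37.7% is a caregiver rate and patient participation is optional, so the patient numbers cannot be derived from it.
- *That the Background repeats the error.* There "Hence, we are now conducting a fully powered randomized trial of the Cornerstone intervention" follows the account of the 63-caregiver pilot and is general background wording.

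**Conclusion.** The sentence is wrong as written. At 37.7% dropout, 147 per group leaves about 92 completers, which is 11 short of 103 and 28 short of 120. The target protects 103 up to about 30% dropout and 120 up to about 18%. These results need only the article's own figures.

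The effect on power is modest and conditional. Power for d = .37 is about 74% if dropouts supply no follow-up data, and 80% or more only if roughly 27 to 30% or more of them supply week-12 data and the effect is constant. These power figures rest on an inferred formula (two-sided α = .025, ρ = .5, mean of two follow-ups minus baseline), which gives 104 to 105 against the stated 103. The base size, the effect size and the planned analysis are not called into question by this point.

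**What to change.** Rewrite the recruitment sentence; no additional participants are needed:

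- Remove the claim that 147 per group covers dropout of 37.7%.
- State that 147 per group leaves 103 completers at up to about 30% dropout and 120 at up to about 18%.
- State that at 37.7% dropout about 92 completers per group remain, with power for d = .37 of about 74% if dropouts give no follow-up data. The sponsor should confirm that figure with the formula actually used in its software.
- If the sponsor relies on week-12 data from later dropouts to hold 80%, state the assumed share (roughly 27 to 30% or more) and the constant-effect assumption.

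The cost is one restated sentence and a less favourable stated power at the worst-case dropout. Should the sponsor prefer to keep the 37.7% claim on completers alone, the target would have to be 166 per group to hold 103 (332 in total) or 193 per group to hold 120 (386 in total).
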